**Figure 3 F3:**
[figure not shown]
Thai LHS trial design. LHS, learning health system. MoPH, Ministry of Public Health

The economic evaluation will be developed from the perspective of the Thai healthcare system and use Thai unit costs. It will include costs of staff time and other resources involved in implementation and maintenance of LHS QI programme (outside PCU staff), including development and maintenance of the Active Patient link (APL) tool, staff training, facilitation visits and other QI-related activities. In addition, PCU appointments, medications, investigations, hospital attendances and admissions of patients with target conditions will be identified using EHR data and costed. The overall additional costs, including the LHS QI programme and patient healthcare, per additional patient achieving target disease management outcome with QI programme compared with usual care will be reported.

This realist evaluation will triangulate the outcomes from the trial and economic evaluation with its own data collection. We use a realist approach because it acknowledges the importance of organisational context and seeks to understand the underpinning mechanisms, rather than make one-size-fits-all judgements.

### Intervention

The LHS intervention has been based on concepts from the model of delivery used by the CEG. The LHS intervention in this context will consist of 3 elements:

**Data management software—the Active Patient Link tool:** to enhance data-driven quality management, the research team has developed the APL tool (figure 4)—an online platform that uses national routine EHR data to visualise actionable quality indicators for frontline healthcare workers. In addition to providing dashboards for performance monitoring, the APL tool includes a recall page that enables clinicians to identify and prioritise patients in their catchment population based on clinical risk. We will iteratively adapt the tool throughout the trial as the staff learn how to use it and will expand its use to more conditions. As many NCD patients present first with HTN, we started with HTN, but we recognise that this frequently co-occurs in people with diabetes, which is why we will focus on diabetes subsequently. Patients with diabetes and HTN are at risk of CKD, and therefore, we will then expand to CKD. As years go on, and if this approach is successful, we anticipate that staff will request add-ons for respiratory, liver and heart disease.At a local level, the use of the tool will vary according to clinical need. PCUs will be able to generate patient lists based on specific clinical criteria to support structured recall; they will be able to view a detailed page of information about the patient’s current medications, laboratory results and clinical observations; and they will be able to identify which patients have been lost to follow-up. The tool therefore supports proactive, individualised care planning and targeted outreach.The feasibility, acceptability and appropriateness of the APL tool and facilitation will be measured through the semi-structured interviews and a short survey. The survey has been devised to capture aspects of tool usability that are not covered by the interviews.**Facilitation support:** to foster sustainable change and embed QI into everyday practice, structured facilitation support through both online and in-person engagements is being provided for the 16 intervention PCUs. Trained facilitators—a doctor, nurse and psychologist—will engage frontline workers in regular meetings to build capacity, offer tailored guidance and co-reflect on local data insights generated by the APL tool. These meetings will occur every 2 weeks, or within a time frame that suits the needs of the PCU. These facilitation sessions will serve multiple purposes: helping frontline staff interpret quality indicators, identify areas for improvement, plan and implement change ideas, and navigate operational challenges. This will ensure that frontline teams remain supported, engaged and empowered throughout the quality improvement cycle, reinforcing a culture of learning and accountability within primary care settings. The facilitation will remain in place for participating PCUs throughout the entirety of the study period.**Education around embedding a culture of quality improvement into clinical practice:** the research team will conduct stakeholder consultation workshops with frontline healthcare workers from 16 sites over the 4-year trial period. The ‘stakeholders’ in question are nurse practitioners, public health officers, primary care physicians and governmental stakeholders such as the Ministry of Public Health and the local provincial public health office. These workshops happen once yearly, introducing the concept of a LHS, providing the research team with an understanding of routine clinical workflows, identifying gaps in the management of NCD cases and helping frontline staff collaboratively design actionable quality indicators. After a year of implementing LHS strategies, the 16 intervention sites will serve as community champions—sharing their lessons learnt, successful strategies and practical experiences with other practices across their province.Additionally, findings from the workshops will be reinforced during the facilitation support visits by the research team to ensure contextual understanding, build trust with local staff, validate findings from the workshops and support the co-design of tailored quality improvement strategies aligned with each site’s needs and capabilities.

**Figure 4 F4:**
[figure not shown]
Screenshot of the APL tool for hypertension. CKD, chronic kidney disease. APL, Active Patient Link. DLP, dyslipidaemia. HDL, high-density lipoprotein. LDL, low-density lipoprotein. CID, citizen ID . eGFR, estimated glomerular filtration rate.

## Methods

### Study design

The evaluation will use mixed methods to provide information about contexts and mechanisms that enable the testing and refinement of programme theories. Qualitative data collection will involve gathering relevant documents and conducting semi-structured interviews to complement the quantitative data and provide insights into the barriers and facilitators of implementing LHSs. Quantitative data collection will involve access to existing EHR sources used for analysis of outcomes for other studies evaluating the LHS intervention and QI activity metrics. The evaluation will be reported according to Realist and Meta-narrative Evidence Synthesis: Evolving Standards guidelines.^32^

### Semi-structured interviews

Semi-structured interviews will be conducted at each intervention site with key staff members. We will perform up to 18 interviews at 3-month to 6-month intervals throughout the study period, between 2025 and 2028. Participants will include PCU-based clinicians and administrative staff, provincial public health office staff, village health volunteers and hospital directors and managers from the intervention sites. Participants will be recruited as per local practice, through local clinical and administrative networks with CMU. Participant consent will be documented prior to interview. The interview topic guide will be informed by the IPT and will be structured to elicit data relevant to contexts (C), mechanisms (M) and outcomes (O). Interviews will gather data on how specific features of the LHS are experienced in organisational and professional contexts. Key areas will include the following:

Contextual factors influencing implementation, including organisational culture, leadership structures, workload pressures and existing approaches to quality improvement.How improved access to patient-level EHR data and the APL tool interacts with local workflows and professional roles.Responses to training and facilitation support, including how these influence confidence, motivation, trust in data and perceived ownership.Perceived short- and medium-term changes in clinical practice, team dynamics and follow-up processes.

### Participant surveys

Prior to the semi-structured interviews, participants will be asked to fill in a short survey, focusing on tool feasibility, usability and appropriateness within staff daily workload. This survey will complement the content of the semi-structured interviews which will focus on wider factors related to intervention implementation. The semi-structured interview guide is included in online supplemental file 2. Tool uptake will be recorded through a user-log using HDC data tracking user log-ins.

### Documents analysis

Key local documents, such as board reports and meeting minutes, will be analysed to understand the outputs of QI activities. Eligible sites will include PCUs that carry out 6 monthly key performance indicator meetings and who have existing documentation from these meetings. Documents will be identified through existing key stakeholder networks with the CMU family medicine department. One to two documents will be analysed per intervention site, depending on their length and scope. We will also review the Public Health District office 3 monthly meeting minutes that have appropriate scope over PCU activity. These documents will provide us with a broader overview of the socio-political context in which the LHS is operating and how the LHS potentially impacts service planning for NCD patient populations.

### Quality improvement outcome and activity metrics

We will explore the main intervention outcomes per site and over time to gain an understanding of which sites had the largest and smallest improvements for different outcomes. We will collect data across three phases:

Phase 1: HTN

The proportion of adults with HTN whose blood pressure meets target levels (<140/90 mm Hg) at 12 months, 24 months and 36 months.

Phase 2: type 2 diabetes

The proportion of adults with T2DM whose blood glucose meets target levels (<6.5%/48 mmol/mol) at 12 and 24 months.

Phase 3: CKD

The proportion of adults with CKD stages 1–4 who are tested for albuminuria at 12 months.

These clinical outcomes will be combined with our qualitative data findings to shed light on some of the mechanisms that could potentially lead to these outcomes: increased access to data through consistent and supported use of the LHS intervention (M) that leads to better HTN control (O).

We will also explore numbers of patients being lost to follow-up as an indirect outcome of the efficacy of the tool. These data will be analysed descriptively alongside the baseline and outcome data to quantitatively explore sites with most/least activity and largest/smallest improvements:

Phase 1: the proportion of patients with HTN with follow-up classified as:

Complete/on-time: patients who attend appointments every 6 months for their HTN review within a 12-month period.Delayed: patients who have routine review appointments for HTN booked later than scheduled within a 12-month period.Lost: patients who are lost to follow-up without an appointment scheduled for routine HTN review within a 12-month period.

Phase 2: the proportion of patients with type 2 diabetes with follow-up classified as:

Complete/On-time: Patients who attend appointments every 6 months for their type two diabetes review within a 12 month period.Delayed: Patients who have routine review appointments for their type two diabetes booked later than scheduled within a 12 month period.Lost: Patients who are lost to follow-up without an appointment scheduled for routine type two diabetes review within a 12 month period.

Phase 3: the proportion of patients with CKD stages 1–4 with follow-up classified as:

Complete/on-time: patients who attend appointments every 6 months for their CKD stages 1–4 review within a 12-month period.Delayed: patients who have routine review appointments for their CKD stages 1–4 booked later than scheduled within a 12-month period.Lost: patients who are lost to follow-up without an appointment scheduled for routine CKD stages 1–4 review within a 12-month period.

The QI activity metrics that will be used within the realist evaluation include:

Number and frequency of clinical team meetings in each intervention site.Frequency of scheduled review of national KPIsNumber and professional roles of participants in these meetings.Number of individuals trained in using the APL tool in the context of QI and their professional roles.Quantitative feedback from training sessions—using a tool developed to collect feedback both for the tool development and facilitation training sessions.Total number of datasets used for QI projects.Volume of missing data within these datasets.

Data collection methods for these metrics will be driven by local practice around documentation of team activity—usually this is in the form of 6 monthly meetings with the provincial public health office. Baseline data for chosen metrics will be compared with data collected after a minimum of 3 months. This data will support the development of potential mechanisms as part of the programme theory; helping to triangulate service planning and quality improvement activities with staff perceptions of the LHS intervention.

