**Methods and analysis:**

A mixed-methods realist evaluation will run in parallel with an interventional trial [Reg No: NCT06873243] in Northern Thailand which aims to improve the management of hypertension (HTN), type 2 diabetes mellitus (T2DM) and chronic kidney diseases (CKDs) using a data-supported learning health systems approach. As part of the trial, 16 primary care units (PCUs) in Chiang Mai and Lamphun provinces will be randomly selected to receive a learning health system intervention to support quality improvement for care of HTN, T2DM and CKD. Performance will be compared between intervention PCUs and all other PCUs in the region. Participants of the realist evaluation will include clinical and other professional staff involved in the development and implementation of the LHS. This realist evaluation will use both quantitative and qualitative data, including semi-structured interviews, surveys and documents from participating sites. Quantitative and qualitative findings will be systematically integrated to test, refine and validate context-mechanism-outcomes to identify consistencies, contradictions and explanatory mechanisms as part of a final programme theory for the successful implementation of the LHS.

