### Non-communicable disease management in Thailand

Most NCD cases in Thailand are managed in primary care units (PCUs), which function as the frontline for the district health system.^8^ PCUs are responsible for screening, diagnosis, treatment initiation, long-term follow-up and prevention activities.^8^ Care delivery in PCUs is led by multidisciplinary teams, including nurses, public health technical officers, general practitioners (GPs) and village health volunteers.^8^ Typically, each PCU has around three to five staff and is mainly operated by nurses. Most PCUs work under district hospitals, with GPs rotating to PCUs once a month on a NCD clinic day.^9^ One PCU covers a population of approximately 10 000.^8^

While this team-based model provides strong structural foundations for chronic care management, PCUs operate as complex adaptive systems. Differences in staffing, leadership, workload, digital literacy and community context create substantial variation in how care is organised and delivered, which then affects PCU clinical performance outcomes.^9^,^13^ Furthermore, clinical audits suggest that variation in clinical performance outcomes reflects availability of healthcare resources and varying degrees of diagnostic and treatment inertia.^9^

In Thailand, electronic health record (EHR) data is used by the Ministry of Public Health to understand how whole regions deliver care.^14^ Health data from all public healthcare facilities in Thailand is uploaded to the central government via the Health Data Centre (HDC) and visualised through the HDC online dashboard.^14^ While this national system offers an overview of population health and facility performance, data is primarily collected for administrative reporting rather than local learning.^15^ Consequently, improvements in NCD outcomes are uneven across facilities, suggesting that availability of data alone is insufficient to drive quality improvement (figure 1).

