#### Rationale for using realist evaluation

The LHS approach has been used internationally, with modification for differing health and care system contexts.^28^ This study will complement a LHS cluster randomised trial (RCT) and the economic evaluation that will occur in parallel. An illustration of the RCT design is included in figure 3. Random sampling has been used to allocate 16 PCUs from 419 total eligible PCUs to receive the intervention (273 units in Chiang Mai and 146 units in Lampang). This intervention is an open-label trial, as those receiving the intervention are aware of their allocation. The full details of the trial are described elsewhere.^27^ The data required for the quantitative outcomes will be collected from the EHR used in Thailand across Chiang Mai and Lamphun provinces, between 2025 and 2028, for the total population registered across the intervention PCUs for the RCT and economic evaluations.

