### Data analysis

Quantitative data will help identify where outcomes occur, while qualitative data will explain how and why these outcomes are achieved, providing a richer understanding of the relationships between contexts, mechanisms, and outcomes. This mixed methods approach will involve:

Comparing data types—quantitative patterns will be triangulated with qualitative insights to identify consistencies, contradictions and explanatory mechanisms.Iterative refinement of context-mechanism-outcome (CMO)—quantitative data will help identify where outcomes occur, while qualitative data will explain how and why these outcomes are achieved, providing a richer understanding of the relationships between contexts, mechanisms, and outcomes.

Where possible we will analyse mixed methods data concurrently to allow thematic sampling of themes within the interviews. Using the CMOs we will develop a final programme theory.

Interview data and documents will be coded using a realist logic of analysis. A reflexive diary will be kept during the qualitative analysis. Methodological rigour and validity will be maintained by having 10% of transcripts independently coded by another researcher. The qualitative data will be examined for CMO configurations, with a particular focus on the (C) and (M): does improved access to data and facilitation support within a collaborative environment (C) provide staff with the tools to adopt data-driven interventions and embed quality improvement culture in their daily clinical care (M)?

Our quantitative data analysis will include outcomes relating to improvements in population NCD burden and consistent use of improvement methodology in clinical care. An initial exploratory review of whether QI activities form a part of the PCU workload will be carried out. We will then perform a baseline analysis both for PCU demographics and their baseline QI activity, to be able to measure change in the outcomes.

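### Per-site improvement in the 16 intervention PCUs is read with no yardstick for chance or regression to the mean, though the comparator PCUs could supply one

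*Protocol article*

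**What the plan says.** The Protocol article, section Quality improvement outcome and activity metrics, takes the main outcomes per site and over time "to gain an understanding of which sites had the largest and smallest improvements for different outcomes". For the follow-up data it adds: "These data will be analysed descriptively alongside the baseline and outcome data to quantitatively explore sites with most/least activity and largest/smallest improvements". Data analysis then gives the quantitative side its role: "Quantitative data will help identify where outcomes occur, while qualitative data will explain how and why these outcomes are achieved". The context-mechanism-outcome configurations refined in this way lead to the final programme theory, which the Ethical approval section names as the evaluation's main outcome.

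Nowhere is a site's change given an interval, shrunk, adjusted for the site's starting outcome level or set against PCUs outside the intervention. The baseline analysis in Data analysis concerns PCU demographics and QI activity.

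A reference group exists in the trial. The Rationale section says "Random sampling has been used to allocate 16 PCUs from 419 total eligible PCUs to receive the intervention" and then splits the eligible total by province as "273 units in Chiang Mai and 146 units in Lampang". The Abstract says "Performance will be compared between intervention PCUs and all other PCUs in the region". The site-level look is not the only evidence: "This realist evaluation will triangulate the outcomes from the trial and economic evaluation with its own data collection", and that data collection includes interviews, surveys, tool log-ins, documents and QI activity metrics.

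**The concern.** Sixteen observed changes always have a largest and a smallest, even if the intervention acts identically everywhere. Two artefacts shape that order. Sampling error spreads the observed changes, more so where a PCU has few patients with the condition. Regression to the mean makes sites with a low baseline tend to rise and sites with a high baseline tend to fall.

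The second artefact matters particularly here. A statement that the approach works best where control was poor at the start is the kind of context finding a realist evaluation looks for, and it could arise without any intervention effect. The qualitative work cannot remove this risk, because it is asked to explain the quantitative pattern. Contexts and mechanisms could then be attached to site differences that are not real.

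**Working it through.** **Count check.** 273 + 146 = 419 eligible PCUs, as stated. 419 − 16 = 403 others. The article gives no site-level precision figure to reproduce.

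**Inputs.** Sites ranked: 16 (Rationale section). Catchment: "One PCU covers a population of approximately" 10 000 people. The rest are assumptions, because the article does not state them: patients per PCU with the condition, n = 100 to 2,000; proportion at target, p = 0.5 (largest variance); correlation between a site's two measurements from shared patients, rho = 0 or 0.5; SD of true site changes, tau = 2, 5 or 10 points.

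**Chance spread.** The standard error of a site's change is sqrt(2p(1−p)(1−rho)/n). The expected gap between the largest and smallest of 16 independent normal values is 3.53 standard errors (simulation). For n = 500 and rho = 0: sqrt(2 × 0.25/500) = 3.16 points, and 3.53 × 3.16 = 11.2 points.

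**Reliability of the order** is tau²/(tau² + SE²). For n = 1,000, tau = 5, rho = 0: 25/(25 + 5) = 0.83.

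| n per PCU | SE, rho 0 (points) | Best–worst gap with no true differences, rho 0 (rho 0.5) | Reliability, tau 2 / 5 / 10 (rho 0) | Observed best site is truly best, tau 2 / 5 (rho 0) |
|---|---|---|---|---|
| 100 | 7.07 | 25.0 (17.7) | 0.07 / 0.33 / 0.67 | 14% / 28% |
| 300 | 4.08 | 14.4 (10.2) | 0.19 / 0.60 / 0.86 | 21% / 43% |
| 500 | 3.16 | 11.2 (7.9) | 0.29 / 0.71 / 0.91 | 25% / 52% |
| 1,000 | 2.24 | 7.9 (5.6) | 0.44 / 0.83 / 0.95 | 34% / 63% |
| 2,000 | 1.58 | 5.6 (3.9) | 0.62 / 0.91 / 0.98 | 45% / 72% |

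The choice of p matters little: at p = 0.3 or 0.7 the gaps shrink by the factor sqrt(0.21/0.25) = 0.92.

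**Regression to the mean.** With no true change, the slope of change on baseline is −v/(sb² + v). Here v = p(1−p)/n plus any site-by-time variance, and sb is the SD of stable site levels. For sb = 5 points and n = 500: v = 0.0005, so the slope is −0.0005/0.0030 = −0.17. A site starting 10 points below average would then be expected to gain 1.7 points from this alone. Adding an assumed 3 points of site-by-time fluctuation gives v = 0.0014 and a slope of −0.36, or 3.6 points. In the other direction, sb = 10 points, n = 1,000 and no extra fluctuation give a slope of −0.02.

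**What the comparators add.** Under a normal approximation, 403 PCUs estimate the SD of usual-care change with a relative standard error of 1/sqrt(2 × 402) = 3.5%. The 16 sites alone give 1/sqrt(2 × 15) = 18%, and they cannot separate noise from true differences in response. If no site differs from usual care, the chance that at least one of 16 falls outside 95% limits is 1 − 0.95^16 = 56%. With 99.8% limits it is 1 − 0.998^16 = 3.2%.

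**The case against.** A reader might infer that the programme theory rests on a ranking. The documents do not say so. The look at sites is exploratory and descriptive. Interviews are planned at every intervention site and documents are drawn from the intervention sites, neither chosen by outcome, and an initial theory existed before the trial began. The ranking informs the theory alongside other evidence.

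A reader might also infer that the order of sites is mostly noise. That is not established either. The denominators and the true variation are unstated, the Background reports substantial variation between PCUs, and the table shows a reliable order under some plausible inputs. HTN and T2DM are measured more than once, which gives some check on persistence, whereas CKD has only a 12-month measurement. Because the 16 PCUs were randomly selected, regression to the mean distorts the order within them but does not bias their average. Nor is there a planned search of outcome-by-activity correlations, so no multiple-testing charge follows.

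It can be said that shrinkage and limits belong in an analysis plan. Their absence alone would be no finding. But the article itself fixes a descriptive contrast of intervention sites and assigns it the task of locating outcomes, and the objection does not answer that.

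The strongest practical objection concerns the comparators. The Rationale section describes outcome data for people registered at the intervention PCUs. The Strengths section states record access for Lampang and Chiang Mai, while the Abstract and Objectives name Lamphun. The Intervention section has the 16 sites sharing what they learn with other practices after a year. These points limit the remedy and are dealt with in the fix.

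**Conclusion.** The point stands as a worthwhile and inexpensive improvement to a stated method. As planned, the largest and smallest improvers cannot be distinguished from chance and regression to the mean. With 50% at target, independent measurements and no true site differences, a gap of about 14, 11 or 8 points would be expected at 300, 500 or 1,000 patients per PCU. The order becomes fairly reliable (0.83 or more) at 1,000 or more patients if true site changes have an SD of at least 5 points. Smaller PCUs would need larger true differences, for example an SD near 10 points at 300 to 500 patients, or strongly correlated repeat measurements. The plan has no means of telling which case applies. All these sizes rest on assumed denominators, correlation and between-site variation. They show that the question is open, not that the observed differences will be spurious.

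**What to change.** 1. Reconcile two matters first: whether outcome data are extracted for the comparator PCUs (the Rationale section against the Abstract and the Strengths section), and whether the second province is Lamphun or Lampang.

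2. Report each intervention site's change as a baseline-adjusted, shrunken estimate (mixed model or empirical Bayes) with an interval. Display it against the distribution of change in the comparator PCUs, analysed in the same way and allowing for denominator size. There are 403 comparators if all other eligible units are used.

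3. Use wide limits such as 99.8%. Describe sites inside them as not distinguishable from usual-care variation.

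4. Draw site contrasts for refining the context-mechanism-outcome configurations from these estimates, not from raw order.

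5. Take the baseline before each disease phase starts. Give most weight to the 12-month HTN data, because sharing with other practices after one year may contaminate later comparisons.

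Cost: some extra analysis, on comparator data the trial needs anyway for its comparison with all other PCUs, and no new sites or participants. The downside is fewer clear-cut site contrasts.

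### The three follow-up classes rest on different events (attendance, late booking, no booking), so they leave gaps, overlap, and let Lost fall through bookings alone

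*Protocol article*

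**What the plan says.** The section Quality improvement outcome and activity metrics asks for the proportion of patients in each of three follow-up classes. For hypertension they are:

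- "Complete/on-time: patients who attend appointments every 6 months for their HTN review within a 12-month period"
- "Delayed: patients who have routine review appointments for HTN booked later than scheduled within a 12-month period"
- "Lost: patients who are lost to follow-up without an appointment scheduled for routine HTN review within a 12-month period"

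The same three definitions are repeated for type 2 diabetes and for CKD, where the last reads "Lost: patients who are lost to follow-up without an appointment scheduled for routine CKD stages 1–4 review within a 12-month period".

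The same section gives the measure its role: "We will also explore numbers of patients being lost to follow-up as an indirect outcome of the efficacy of the tool". On analysis it says: "These data will be analysed descriptively alongside the baseline and outcome data". The stated purpose is to see which sites had the most and least activity and the largest and smallest improvements.

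The Intervention section describes what the Active Patient Link tool does. On recall: "PCUs will be able to generate patient lists based on specific clinical criteria to support structured recall". On patients who have dropped out of care: "they will be able to identify which patients have been lost to follow-up".

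**The concern.** Each class is triggered by a different event. Only Complete requires that a patient was seen. Delayed depends on when a review was booked, and Lost on whether one was booked at all. Lost is also partly circular, because it uses loss to follow-up to define itself. No rule covers a missed appointment, and no order of precedence is given where two classes apply.

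Two things follow. First, the three proportions need not add to 100%, and two analysts could code the same records differently. Second, the intervention acts on the event that defines Lost. The tool shows staff who is lost and helps them recall those patients. A booking that results takes the patient out of Lost while it stands, whether or not the patient comes.

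The evaluation uses quantitative patterns to locate where outcomes occurred and qualitative data to explain them. A fall in Lost that reflects bookings without visits could send that explanatory work after an improvement in care that did not happen.

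**Working it through.** The article gives no figure for this measure, so there is nothing to reproduce. The check applies the printed definitions to every combination of attendance and booking.

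**Inputs.** Attendance over 12 months: every 6 months, some reviews, none. Booking: as scheduled, later than scheduled, none. That gives 3 × 3 = 9 patterns. The wording of Lost allows two readings:

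- Reading A: having no appointment is enough.
- Reading B: no appointment and not seen at all.

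| Attended | Booking | Reading A | Reading B |
|---|---|---|---|
| Every 6 months | As scheduled | Complete | Complete |
| Every 6 months | Late | Complete and Delayed | Complete and Delayed |
| Every 6 months | None | Complete and Lost | Complete |
| Some | As scheduled | No class | No class |
| Some | Late | Delayed | Delayed |
| Some | None | Lost | No class |
| None | As scheduled | No class | No class |
| None | Late | Delayed | Delayed |
| None | None | Lost | Lost |

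**Count.**

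- Reading A: 5 patterns in exactly one class, 2 in none, 2 in two (5 + 2 + 2 = 9).
- Reading B: 5 in exactly one, 3 in none, 1 in two (5 + 3 + 1 = 9).

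These are counts of patterns, not shares of patients. The article gives no attendance or booking rates from which shares could be derived.

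**Sequence.** Suppose a missed booking lapses, so that the patient is then either rebooked late or has no appointment. The two unclassified as-scheduled rows disappear and 7 patterns remain. Reading A then has 0 patterns without a class and 2 in two classes. Reading B has 1 without a class (seen at some reviews, nothing booked) and 1 in two classes. The gap shrinks or closes, but the overlap remains.

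**Effect of recall on Lost.** Let L be the share of patients Lost at baseline and s the fraction of them given an appointment, with nobody attending.

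- Lost afterwards = L × (1 − s).
- Change in Complete = 0, because Complete requires attendance.
- The share s × L moves to Delayed if the appointment counts as late, or to no class if it counts as on schedule.

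So Lost falls by the fraction s with no patient seen. Neither L nor s is in the article, so no numerical size is attached.

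**Same check on attendance-only classes.** If the classes are attended at the stated interval, attended at least once but not at that interval, and none attended, each of the 9 patterns falls in exactly one class (3 + 3 + 3 = 9). A booking without a visit then changes no class.

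**The case against.** **A missed appointment has a sequel.** A rebooked patient fits Delayed, and one who is not rebooked arguably has no appointment and fits Lost. This is a natural reading and it stands in part: it rules out the inference that the whole group of non-attenders drops out of the classification. But the article does not say that a missed booking lapses. Even if it does, the overlap remains, and a non-attender rebooked late still counts as Delayed without having been seen.

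**Not everything here is booking.** A reader might infer that the whole measure records booking activity. It does not. Complete requires attendance, and all three proportions are reported. Bookings without visits would show as lower Lost and flat Complete, and the recalled patients would probably appear in Delayed. This stands. It makes the pattern detectable to someone looking for it, but it does not make Lost on its own a sound sign of efficacy.

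**The tool is not said to book.** A reader might picture the tool moving patients out of Lost the instant an appointment is entered. The article says only that it supports recall and identifies lost patients. It gives no timing for updating a class and no automatic booking. The concern needs only that recall leads staff to make bookings.

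**The role is modest.** The measure is exploratory, indirect and descriptive. Site comparison is made alongside baseline and outcome data, then set against interviews. The article does not rank or credit sites on Lost alone, and the blood pressure, glucose and albuminuria outcomes do not depend on these classes. This stands and limits the severity.

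**It is a condensed article.** Coding rules and precedence may be in a fuller document; the section Rationale for using realist evaluation says full trial details are elsewhere. That would excuse silence. Here the definitions are printed, and they do not fit together.

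**Conclusion.** The point holds at moderate severity. For all three conditions the printed classes are neither exhaustive nor mutually exclusive: two or three of nine attendance-by-booking patterns have no class, and one or two have two. A non-attender is not counted as Lost while a booking stands. Lost can therefore fall through bookings alone, in a study whose tool supports recall and whose plan reads loss to follow-up as an indirect sign of that tool's efficacy.

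The conclusion rests on the definitions being applied as printed. The size of the no-class gap depends on two things the article leaves open: whether a missed booking still counts as an appointment, and whether Lost also requires that the patient was not seen. The effect on Lost depends on neither.

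The documents do not support a numerical estimate of the distortion, or a claim that the trial's clinical outcomes are affected.

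**What to change.** Define all three classes on attended reviews within the same 12-month period, keeping the protocol's own review interval:

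- **Complete:** reviews attended at the stated interval.
- **Delayed:** at least one review attended, but not at that interval.
- **Lost:** no review attended, whatever was booked.

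Report bookings and missed appointments separately, as process measures of recall. Apply the same definitions at baseline and at follow-up for all three conditions, so that change within a site is measured on one scale. This point calls for no change to the denominator.

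**Cost.** Some re-coding of visit data from the electronic records. Complete already needs attendance, so no new data source is required. Lost will probably look less favourable, because booked patients who were never seen will be counted in it. The middle class will include patients seen once and not again, so its label should say so. The section Initial programme theory describes the hypertension phase as still being piloted, which leaves time to settle the definitions before the diabetes and CKD phases.
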